#### Process of change

The process of change will be evaluated by a validated scale constructs from the transtheoretical model [61]. The process of change scale is a 22-item self-administrated questionnaire to measure eight process of change: self-reevaluation (item 4,8 and 12), reinforcement management (items 7,15 and 12), self-liberation (items 8, 16 and 22), dramatic relief (items 2 and 10), environmental reevaluation (items 3 and 11), counterconditioning (items 5, 13 and 19), helping relationships (items 6, 14 and 20) and consciousness raising (items 1, 9 and 17). Participants will answer to a Likert scale ranging from 1 (never) to 5 (very often). Items in each process of change will be added and then an average score will be calculated. When the average is ≥3, the process of change is activated.

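### The printed process-of-change key uses items 8 and 12 twice and items 18 and 21 never, so at least one of the eight scores, and most likely two, would be wrong if it is programmed as written

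*Protocol article*

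**What the plan says.** The Process of change section of the Protocol article states: "The process of change scale is a 22-item self-administrated questionnaire to measure eight process of change". It then prints a key that assigns item numbers to every process. The three entries that matter here read "self-reevaluation (item 4,8 and 12), reinforcement management (items 7,15 and 12), self-liberation (items 8, 16 and 22"). For the remaining five processes the key gives 1/9/17 (consciousness raising), 2/10 (dramatic relief), 3/11 (environmental reevaluation), 5/13/19 (counterconditioning) and 6/14/20 (helping relationships).

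Answers run from 1 to 5. The items of a process are summed and averaged, and a cut-off is applied: "When the average is ≥3, the process of change is activated". The scale is described as validated, with a literature reference.

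The Background lists process of change as the thirteenth of fourteen secondary aims. Table 1 schedules the questionnaire at inclusion, M3 and M6. Statistical methods names it among the outcomes whose change from baseline is compared between arms. Nothing else in the article amends the key, or says that some items count towards two processes or are left unscored.

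**The concern.** The article gives the full scoring rule for a secondary outcome, and the rule does not fit the questionnaire it describes. With 22 items and 22 places in the key, each item would be expected once. Instead two items do double duty and two are absent.

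A score built this way no longer measures the process it is named after, because part of its weight comes from an item belonging elsewhere. Scores that share an item are also correlated by construction, which would affect any reading of how the processes move together. The scores would further depart from the validated instrument that the section cites.

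**Working it through.** **Inputs.** All come from the Process of change section: 22 items, eight processes, the item lists, answers from 1 to 5, and the cut-off of 3.

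**Step 1: count the key.** In printed order the processes have 3 + 3 + 3 + 2 + 2 + 3 + 3 + 3 = 22 places, which equals the stated number of items. The different items that appear are 1–17, 19, 20 and 22, which makes 20.

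- Used twice: item 8 (self-reevaluation and self-liberation) and item 12 (self-reevaluation and reinforcement management).
- Never used: items 18 and 21.
- Check: 20 different items + 2 repeats = 22 places; 22 items − 20 used = 2 unused.

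**Step 2: how many scores are affected?** Assume that each item belongs to one process and that the two surplus entries stand where 18 and 21 should be. One use of item 8 and one use of item 12 are then wrong, which gives 2 × 2 = 4 possibilities:

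| Wrong use of 8 | Wrong use of 12 | Scores affected |
|---|---|---|
| self-reevaluation | reinforcement management | 2 |
| self-reevaluation | self-reevaluation | 1 (would become 4, 18, 21) |
| self-liberation | self-reevaluation | 2 |
| self-liberation | reinforcement management | 2 |

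At least one score is wrong in every case, and two are wrong in three of the four.

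**Step 3: what the numbering suggests.** Sorted by lowest item, and with the out-of-place entries left blank, the key reads:

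1/9/17, 2/10, 3/11, 4/12/_, 5/13/19, 6/14/20, 7/15/_, 8/16/22.

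The second item is always the first plus 8. The third items of the six three-item processes run 17, _, 19, 20, _, 22. The gaps are exactly 18, in the process starting at 4, and 21, in the process starting at 7. That gives self-reevaluation = 4, 12, 18 and reinforcement management = 7, 15, 21, with self-liberation unchanged. All 22 items are then used once. This is the first row of the table.

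**Step 4: size for one patient.** In a three-item average each item has weight 1/3. The largest gap between two answers on a 1 to 5 scale is 5 − 1 = 4, so one wrong item shifts the average by at most 4/3 = 1.33.

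An illustration under the step 3 reading: a patient answers 3 on items 4 and 12, 5 on item 8 and 1 on item 18. The printed key gives (3 + 5 + 3)/3 = 3.67, which is activated. The pattern-based key gives (3 + 3 + 1)/3 = 2.33, which is not. The difference is 1.33.

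**Step 5: overlap between scores as printed.** Self-reevaluation (4, 8, 12) shares item 12 with reinforcement management (7, 15, 12) and item 8 with self-liberation (8, 16, 22). Reinforcement management and self-liberation have no item in common.

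**The case against.** The strongest reply is that this is a misprint in an article and not a flaw in the analysis. An 8 for 18 is a dropped digit, and a 12 for 21 is two digits reversed. The section cites a validated scale, and a programmer may well take the key from that source. The article does not say that its sentence is the scoring specification. This stands in part: the harm is conditional on the printed key being used. It does not remove the point, because the article states the rule in full, states it wrongly, and corrects it nowhere.

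Four stronger readings are tempting but not supported:

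- *That two scores are shown to be wrong.* Only the repeats and omissions are certain. Which scores are affected is inferred from the numbering, and the source scale is not at hand.
- *That both suspect scores become entangled with self-liberation.* Only self-reevaluation shares an item with it.
- *That 1.33 points measures the effect on the trial's comparison.* It is the extreme for one patient and one wrong item. The same key would apply to both arms and all visits, and nothing in the article implies that scoring would differ by arm. Nor does Statistical methods list a separate analysis of activated status.
- *That data would be lost.* No printed rule stops items 18 and 21 from being collected. If the answers are stored, the scores can be recomputed before analysis.

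It is also fair to say that the stakes are limited. This is one of many secondary aims, and the alpha is divided between the two co-primary endpoints only.

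**Conclusion.** The concern holds for the key as printed. The tally is exact: 22 places, 20 different items, 8 and 12 repeated, 18 and 21 missing. If the key is programmed as written, and if each item belongs to one process, at least one of the eight scores is wrong. Most likely two are, self-reevaluation and reinforcement management, each with one of its three items replaced. Two of the 22 answers would go unused.

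The consequence is that what the affected subscales measure is contaminated, and some individual patients could be misclassified on activation. No bias between arms is shown. The co-primary endpoints and the sample size are untouched. The point deserves correction because it concerns a stated rule for an outcome that is compared between arms.

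**What to change.** Check the item key against the cited validated scale and correct the line in the protocol and wherever it is repeated in the analysis plan. The numbering points to self-reevaluation = items 4, 12, 18 and reinforcement management = items 7, 15, 21, with 8, 16, 22 kept for self-liberation. Treat this as a proposal until the source confirms it.

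In the scoring program, add a check that each of the items 1 to 22 is assigned to exactly one process, and confirm that all 22 answers are stored. If any scores have already been derived with the printed key, recompute them before the arms are compared.

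The cost is one corrected line and a short program check. No change to data collection, sample size or the primary analysis is needed.

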#### Personality

Based on the Five-Factor Model [62], personality traits will be assessed by the French Big Five Inventory questionnaire (BFI-Fr). The BFI-Fr contains 45 self-descriptive statements that assess the 5 personality traits: neuroticism (which refers to a propensity to experience negative emotions, distress, and anxiety), extraversion (a propensity to be energetic, sociable, and experience positive emotions); openness to experience (the tendency to be curious, imaginative, and to entertain new ideas, values, and experiences); conscientiousness (reflecting self-disciplined, planful, and organized); and agreeableness (which refers to cooperativeness and altruism). Each item was rated on a 5-point Likert scale ranging from 1 (strongly disagree) to 5 (strongly agree). All items will be recoded in the direction of the trait label, and the mean will be taken across items for each personality trait.

#### Cancer-related cognitive impairment

The cancer-related cognitive impairment will be measured by the Functional Assessment of Cancer Therapy—Cognition (FACT-Cog) [63]. The FACT-Cog is a validated self-administrated questionnaire in order to assess memory, attention, concentration, language, and thinking abilities. The questionnaire is composed of 37 items with four subscales: patients’ perceived cognitive impairments, perceived cognitive abilities, deficits observed or commented on by others, and impact of cognitive changes on HRQoL. Participant will answer how often this situation occurred during the last 7 days on a Likert-type scale ranging from “never” to “several times a day”. For both scales, higher scores indicated better perceived cognitive function.

#### Satisfaction

A self-developed questionnaire with 21-item will evaluate satisfaction concerning the use of connected devices (application, website, quizz, activity tracker) for the intervention group.

### Statistical analysis

#### Sample size

The study design was based on Burris et al. [64] using the time to deterioration (TTD) on the EORTC QLQ-C30 with comparable population and treatment for the global HRQoL (primary objective) and fatigue symptom domain (co-primary objective).

The overall two-sided alpha of 0.05 will be split among the co-primary endpoints, with 0.04 for time to definitive deterioration of HRQoL (TTD1) and 0.01 for time to definitive deterioration of fatigue (TTD2). We estimate that about 244 randomized participants with a minimum of 189 deterioration events observed will be required to achieve a 90% statistical power to detect an improvement in median TTD1 from 8 (control) to 13 months (intervention) (HR = 0.615), using a two-sided alpha of 0.04, and assuming a 30-month accrual and 18-month follow-up, and an 1% exponential dropout rate. This sample size will permit to detect the same improvement in median TTD2 from 8 to 13 months with a 77% power and using a two-sided alpha of 0.01 (nQuery Advisor V7.0).

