### Evaluations

#### Modalities

All patients will benefit from four face-to-face assessments, when attending the participating hospital center for their regular oncology follow-up visit:an initial assessment at inclusion before the start of the first line of chemotherapy (or up to 1 month after the start of chemotherapy) (Baseline), a second assessment 3 months after inclusion (halfway through the intervention) (M3), a third assessment 6 months after inclusion (i.e., at the end of the intervention) (M6) and a fourth assessment 12 months after inclusion (6 months after the end of the intervention) (M12). During these face-to-face assessments, a PA instructor will perform the physical assessments and the anthropometric measurements and a blood sample will be taken. In case of first tumour progression during the study, an additional blood sample will be taken.

All participants will also have to complete questionnaires directly via the mobile application or on the website “ABLE02” every 6 weeks until W24 and then every 12 weeks until W48 (Inclusion, W6, W12, W18, W24, W36, W48) and then 18 months after inclusion. At each time point, the participant will be notified that a new questionnaire is available and must be completed. If a participant does not complete a questionnaire, a second notification will be sent 1 week after the initial notification. Participants encountering difficulties to fill in a questionnaire have possibility to contact the clinical research assistant. Questionnaires not completed by a participant will be automatically deleted after 6 weeks. The clinical research assistant will track questionnaire completion via the ABLE02 professional dashboard to limit missing data and will have the possibility to enter directly questionnaire data collected by phone or face-to-face via the internet dashboard to help patients who meet difficulties.

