**Self-reported outcomes**									
Quality of life (QLQ-C30)	X	X	X	X	X	X	X		
Physical activity level (GODIN)	X		X		X		X		
Undernutrition and dietary patterns	X				X				
Fatigue (QLQ-FA12)	X		X		X		X		
Sleep quality (PSQI)	X				X				
Taking medicines and dietary supplements	X		X		X		X		X
Lifestyle	X								
Acceptability ABLE02					X				
Transtheoretical model behaviour change	X		X		X				
Personality traits (BFI)	X				X				
Cancer-Related Cognitive Impairment (FACT-Cog)	X				X		X		

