#### Statistical methods

Analyses will be performed on the intention-to-treat (ITT) population including all randomized participants analyzed according to the randomization scheme. Due to the lack of data (HRQoL) studies, a sub-population will be defined for the analysis of HRQoL, corresponding to a modified ITT population, i.e., all ITT patients with at least the available HRQoL score at baseline.

Qualitative variables will be described using frequency and percentage distributions. The number of missing data will be given, but will not be considered for the calculation of proportions.

Quantitative data will be described using the number of observations, mean, standard deviation, median, minimum and maximum values.

For the primary endpoint analysis, the time to definitive deterioration (TTD) will be defined as the time interval since randomization to the observation of the first deterioration (decrease for global HRQoL score and increase for fatigue score) of 5 points at least as compared to the baseline score, with no further improvement of 5 points at least as compared to the baseline score [49, 64]. Patients with no deterioration observed during the study will be censored at the time of the last available score. Patients with no follow-up score will be censored 1 day after their inclusion. If a deterioration is followed by missing data, this deterioration will be considered as definitive. TTD will be estimated using the Kaplan-Meier method and compared between groups with a log-rank test, stratified by the presence of visceral metastases, the method of administration of chemotherapy and the 6MWD, at a two-sided significance level of 0.04 (TTD1) or 0.01 (TTD2). Univariate and multivariate Cox regression models will be performed to explore factors influencing the TTD.

Sensitivity analysis will be performed to assess 10-point deterioration in global HRQoL score and fatigue in comparison with baseline. Sensitivity analysis will also be performed including death as an event.

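### The 244 women, 189 events and 90%/77% power reproduce only with 18 to 48 months of deterioration follow-up per woman, which the QLQ-C30 schedule does not supply

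*Protocol article*

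**What the plan says.** The Sample size section asks for "about 244 randomized participants with a minimum of 189 deterioration events observed", a number that "will be required to achieve a 90% statistical power" for TTD1 when the median rises from 8 to 13 months at a two-sided alpha of 0.04. The same sample is said to detect the same difference in TTD2 "with a 77% power and using a two-sided alpha of 0.01". The calculation is made "assuming a 30-month accrual and 18-month follow-up, and an 1% exponential dropout rate". The unit of the 1% is not given.

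The data for both endpoints come from the QLQ-C30. Two places fix when it is collected:

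- Evaluations, Modalities: after the six-weekly phase, questionnaires are completed "every 12 weeks until W48 (Inclusion, W6, W12, W18, W24, W36, W48) and then 18 months after inclusion".
- Table 1, row "Quality of life (QLQ-C30"): seven marks, from inclusion to the M12/W48 column, and none in the M18 column. The only entry at M18 is survival, in the clinical data row.

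Statistical methods adds the censoring rule: "Patients with no deterioration observed during the study will be censored at the time of the last available score". Death counts as an event only in a sensitivity analysis.

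**The concern.** Accrual over 30 months followed by 18 more months of follow-up normally means that the first woman is observed for 48 months and the last for 18. A time-to-event sample size then credits the trial with events up to that common cut-off. Here an event exists only where a QLQ-C30 score exists, and each woman's series stops at a fixed time after her own inclusion: 18 months by the text, about 11 to 12 months by Table 1. Calendar time after a woman's last form adds no events.

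The two places also disagree on when the last primary-outcome score is taken, and that decides how large the shortfall is. If the stated figures stand, a null result on either co-primary endpoint would be read as better powered than the design makes it.

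**Working it through.** **Inputs.** Medians 8 and 13 months, HR = 8/13 = 0.615, two-sided alpha 0.04 (TTD1) and 0.01 (TTD2), power 90% and 77%, N = 244 (122 per arm), accrual 30 months, follow-up 18 months, dropout 1% (all Sample size, with 1:1 allocation from Randomization). Last QLQ-C30: 18 months (Modalities) or M12/W48 (Table 1). Visit windows of ±1 month at M12/W48 and M18 (Table 1). Assumptions: exponential event and dropout times, uniform accrual, dropout between none and 1% per month.

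**Step 1, the stated events and power.** Schoenfeld: d = 4(z₁₋α/₂ + z₁₋β)² / (ln HR)² = 4(2.054 + 1.282)² / 0.4855² = 188.8, so 189. Power = Φ(√d/2 × 0.4855 − z₁₋α/₂). With d = 189 this is 90.0% at alpha 0.04 and 77.7% at alpha 0.01. The plan's figures are reproduced.

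**Step 2, the stated N.** Hazards are λ = ln2/8 = 0.0866 and ln2/13 = 0.0533 per month, and the dropout hazard is η. With k = λ + η, accrual A = 30 and further follow-up F = 18,

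P(event) = (λ/k) × [1 − (e^(−kF) − e^(−k(F+A)))/(kA)].

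With η = 0.01 per month this gives 0.845 and 0.721. Expected events are 122 × (0.845 + 0.721) = 191, and 189 events need N = 189/0.783 ≈ 241, close to 244. Other readings fit worse:

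- 18 to 48 months with 1% per year, or 1% overall: N ≈ 219 to 220.
- 18 months for every woman: N ≈ 269 (no loss) to 288 (1% per month).

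**Step 3, the schedule described.** With a fixed end t for each woman, P(event) = (λ/k)(1 − e^(−kt)) and events = 122 × (P_control + P_intervention). For example, t = 18 and η = 0.01 give 0.739 and 0.573, so 160 events.

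| Last QLQ-C30 | Events (1%/month to no loss) | Power TTD1 | Power TTD2 |
|---|---|---|---|
| W48 (11.04 months) | 123–129 | 74–76% | 55–57% |
| 12 months | 130–137 | 76–78% | 57–60% |
| 13 months (upper window) | 136–143 | 78–80% | 60–63% |
| 18 months | 160–172 | 84.5–87% | 69–73% |
| 19 months (upper window) | 164–176 | 85–88% | 70–74% |
| Plan: 18–48 months, 1%/month | 191 | 90% | 78% |

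Even the most favourable fixed schedule, with no loss and every last form at 19 months, gives 176 events.

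**The case against.** **The milder schedule has more support in the text.** Modalities names an 18-month questionnaire, and the abstract lists M18 among the main assessments, covering psychological parameters as well as survival. That is fair, though neither place names the QLQ-C30 at M18, and the Data collection section presents Table 1 as the complete schedule. If the M18 form is collected, the TTD1 loss is only about 3 to 5.5 points.

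**Follow-up of 18 months may mean 18 months per woman.** The schedule in the text would then match, but N would not: 189 events need about 269 to 288 women. The inconsistency moves and does not vanish.

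**The range of 18 to 48 months and the monthly dropout unit are not written in the protocol.** Correct. They are inferred because they bring N near 244. The shortfall in Step 3 does not depend on the unit, since it holds down to zero loss.

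**A shorter schedule may create events.** A deterioration on the last form has no later form to reverse it, and a deterioration followed by missing data counts as definitive. Ending collection early could therefore label more deteriorations as definitive and push the counts above those in the table. This stands as a caveat. The documents do not allow its size to be worked out, and the plan's calculation does not invoke it.

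**Stronger readings that the documents do not support.**

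- A reader might infer that 189 events can never be reached. The arithmetic shows only that they are not expected under the planning assumptions.
- A reader might infer that the intervention median will be inestimable if W48 is last. The expected event-free share is 55.5% at W48, 52.7% at 12 months and 50% at 13 months, so the median could still be reached by chance or within the window. The log-rank test does not need it.
- A reader might infer that the 1% leaves out deaths. The Sample size section does not say what dropout covers, and no higher loss rate can be taken from the documents.

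**Conclusion.** The inconsistency is real. The arithmetic of the plan is internally correct, but it rests on a length of observation for the endpoint that the questionnaire schedule does not provide. Under the plan's own medians, N = 244, exponential times and loss between none and 1% per month:

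- Last form at 18 months: about 17 to 29 events short of 189 (189 − 172 and 189 − 160). The power loss is moderate: about 3 to 5.5 points for TTD1, and about 4 to 8 points for TTD2 against the stated 77%.
- Last form between W48 and 12 months: about 52 to 66 events short (189 − 137 and 189 − 123). TTD1 power falls by about 12 to 16 points, and TTD2 power is 55–60%.

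Which case applies turns on a contradiction between Modalities and Table 1 that the document does not resolve. Either way, the stated event count and both stated powers do not belong to the schedule as described.

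**What to change.** 1. Reconcile Modalities with Table 1 on whether the QLQ-C30 is collected at M18. Marking it in the M18 column gives the smaller loss of power.
2. State the length of observation per woman and the unit of the 1% dropout rate.
3. Restate the expected events and the power of both co-primary endpoints for the schedule kept, as ranges: about 160–172 events with 85–87% and 69–73%, or about 123–137 events with 74–78% and 55–60%. Note that these assume exponential times.
4. Stop presenting 189 as the number of events that this design will yield. It remains the number needed for 90% power at alpha 0.04.

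Running the in-app questionnaire past 18 months to a common cut-off would match the calculation, but it is optional. It would mean forms for up to 48 months after a 6-month programme and continued staff effort to chase and enter them. It restores the stated power only if the hazard ratio of 0.615 persists long after the programme ends.

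Steps 1 to 4 are changes to text and one table cell. If Table 1 is the version now in use, marking M18 also adds one questionnaire per woman. The main cost is a less favourable stated power.
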